## 7.8 Concomitant Medication

Medications that are considered necessary for the safety and well-being of the subject can be given at the discretion of the investigator, unless otherwise specified as an exclusion criterion.

All medications that the subject has taken regularly during the trial must be recorded in the eCRF. Non prescribed food supplements such as vitamins and anti-oxidants should also be recorded in the eCRF if taken regularly. Any changes need to be reported. Concomitant prescribed medications since start of symptoms shall be recorded at Visit 1.

## 7.9 Treatment after trial end

After an interval of six weeks no more HBO2 must be given. The total dose during the trial will be recorded until six weeks after first treatment. At trial end, the participants will be treated according to routine clinical praxis.

## 8. Handling of Adverse Events

### 8.1 Definitions

#### 8.1.1 Adverse Event (AE)

Adverse Events constitute any untoward medical occurrence in a clinical investigation subject administered a medicinal product and, which does not necessarily have a causal relationship with the treatment, can be an unfavorable and unintended sign (including an abnormal laboratory discovery), symptom or disease temporally associated with the use of the medicinal (investigational) product, whether or not related to the medicinal (investigational) product.

#### 8.1.2 Adverse Reaction (AR)

In the new use of a medicinal product all noxious and unintended reactions to the medicinal product related to any dose should be considered an adverse reaction (AR). The phrase 'reaction to a medicinal product' means that the causal relationship between the medical product and an adverse event is at least a reasonable possibility, that is the relationship cannot be ruled out.

#### 8.1.3 Serious Adverse Event (SAE)

Serious adverse events constitute any untoward medical occurrence that at any dose:

- results in death
- is life-threatening
- requires inpatient hospitalization or prolongation of existing hospitalization
- results in persistent or significant disability or incapacity
- results in a congenital anomaly/malformation
- regarded as medically important without meeting the above mentioned criteria

Medical and scientific assessment will be made to determine if an event is 'serious' and whether it would prompt reporting in other situations, for example important medical events that may not be directly life-threatening or result in death or hospitalization but may compromise the subject or may require intervention to prevent one of the other results set forth in the definitions above. These should also normally be considered as SAEs.

#### 8.1.4 Suspected Unexpected Serious Adverse Reaction (SUSAR)

SUSAR comprise a reaction/event that is unexpected, serious, and suspected to be caused by the treatment, i.e. adverse events that are not included in the SPC.

Trial Code: HOT-LOCO  
Version No: v.4  
Date: 2022-01-03  
EudraCT No: 2021-000764-30

## 8.2 Assessment of Adverse Events

### 8.2.1 Assessment of causal relationship

The investigator is responsible for determining whether there is a causal relationship between the AE/SAE and use of the investigational product.

Those AEs which are suspected of having a relationship to the investigational product will be followed up until the subject has recovered or is well taken care of and on their way to good recovery (see also section 8.4, Follow-up of Adverse Events).

All AEs will be categorized either as related, probably related, possibly related, unlikely related or not related, in accordance with the definitions below:

**Related:** Clinical event, including abnormal results from laboratory analyses, occurring in a plausible temporal sequence in relation to drug administration. The observed event matches with the known adverse reactions scheme for the drug involved. The event cannot be attributed to underlying disease or other medications.

**Probably related:** Clinical event, including abnormal results from laboratory analyses, occurring within a reasonable time after administration of the investigational product. The observed event match with the known adverse reactions scheme for the drug involved. It is unlikely attributable to underlying disease or other drugs.

**Possibly related:** Clinical event, including abnormal results from laboratory analyses, occurring within a reasonable time after administration of the intervention/investigational product. The event could be explained by the investigational product and its emergence is reasonable in relationship with use of the investigational product, but there is insufficient information to determine the relationship. The event could be explained by an underlying disease or other medications.

**Unlikely related:** Clinical event, including abnormal results from laboratory analyses, with a with a temporal relationship with respect to drug exposure that makes a relationship improbable (but not impossible). The event could be plausibly explained by an underlying disease or other medications.

**Not related:** Clinical event, including abnormal results from laboratory analyses that do not meet any of the above criteria for relatedness.

### 8.2.2 Assessment of intensity

Each adverse event shall be classified by an investigator as mild, moderate or severe.

**Mild:** Transient symptoms that are relatively tolerable and does not affect the subject's normal life.

**Moderate:** Marked symptoms, sufficiently unpleasant that interfere with the subject's normal life. Deterioration of function but is transient.

|             |                |
|-------------|----------------|
| Trial Code: | HOT-LOCO       |
| Version No: | v.4            |
| Date:       | 2022-01-03     |
| EudraCT No: | 2021-000764-30 |

**Severe:** Unacceptable or incapacitating symptoms that causes deterioration of function to the extent that the subject is unable to perform normal activities.

### 8.2.3 Assessment of seriousness

The investigator is responsible for assessing the seriousness (serious or non-serious). If the incident is considered serious, this should be reported as a serious adverse event (SAE) by the investigator to the sponsor. See also section 8.3.2, Reporting of Serious Adverse Events (SAE).

## 8.3 Reporting and registration of Adverse Events

At each trial visit, AE are registered. Collection of AE data will start directly after inclusion and continue until 13 weeks (Visit 3) which is 7 weeks after the subject has ended their treatment with the investigational product. All AEs that occur during the trial and that are observed by the investigator/study-nurse or reported by the subject will be registered in the eCRF regardless of whether they are related to the investigational product or not. Assessment of causal relationship, severity, and whether the AE is considered to be an SAE or not will be done by the investigator directly in the eCRF. At minimum, for each AE/SAE, a description of the event is recorded (diagnosis/symptom if diagnosis is missing), start and stop times, causal relationship, severity, if the AE is considered to be an SAE or not, measures and outcome.

The following situations will not be reported as AE/SAE:

- Symptoms judged by the investigator as associated with Long COVID will not be recorded as an AE.
- A change in routine biochemistry will not be reported as AE unless detected during the treatment period.
- Non-serious adverse events outside the treatment period (visit 2) will not be recorded.

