#### 4.4.4 Safety and Compliance Endpoints

- I. Number of subjects, proportion of subjects and number of AEs at 13 weeks.
- II. Number of subjects, proportion of subjects that have completed planned treatments after 6 weeks.

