### **AE and ADR**

Adverse events (AEs) and collection of AEs and Serious Adverse Events (SAEs) data.

|             |                |
|-------------|----------------|
| Trial Code: | HOT-LOCO       |
| Version No: | v.4            |
| Date:       | 2022-01-03     |
| EudraCT No: | 2021-000764-30 |

Collection of AEs will start directly after inclusion and will be recorded until visit 3. Only SAEs will be collected outside the treatment period (visit 2). Ongoing AEs and SAEs at the end of visit 3 will be followed up during long-term follow-up until the subjects last visit. Definitions, documentation and reporting of AEs are described in detail in the AE section below.

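### The safety endpoint counts AEs at 13 weeks, but non-serious AEs are recorded only during treatment, so the count as worded would be incomplete over a window that differs by subject

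*Protocol*

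**What the plan says.** The endpoint in section 4.4.4, repeated in the synopsis, is "Number of subjects, proportion of subjects and number of AEs at 13 weeks". Section 8.1.1 defines an AE as "any untoward medical occurrence in a clinical investigation subject administered a medicinal product", whether or not it is related to treatment and with no restriction to serious events.

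Several places call for recording through visit 3:
- Section 8.3: "Collection of AE data will start directly after inclusion and continue until 13 weeks (Visit 3"), and the same sentence adds "which is 7 weeks after the subject has ended their treatment with the investigational product".
- Section 8.3, next: "All AEs that occur during the trial and that are observed by the investigator/study-nurse or reported by the subject will be registered". Causality plays no part in this rule.
- Section 5.2.1, AE and ADR: collection from inclusion until visit 3.
- Table 1 marks AE/ADR at every visit, and the visit 3 procedures have adverse events reviewed and recorded.

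Two places take the non-serious part back:
- Section 5.2.1, AE and ADR, in the next sentence: "Only SAEs will be collected outside the treatment period (visit 2").
- Section 8.3, in its list of situations not reported: "Non-serious adverse events outside the treatment period (visit 2) will not be recorded".

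The same list contains two further exclusions. Changes in routine biochemistry count only if detected during the treatment period. The other reads: "Symptoms judged by the investigator as associated with Long COVID will not be recorded as an AE".

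**The concern.** The endpoint covers AEs of any seriousness over 13 weeks, while the recording rules keep non-serious events only for the part of that time in which the subject is being treated. A table built from such data and labelled with week 13 would mix SAEs to week 13 with non-serious events over a shorter period. The length of that period depends on how each subject's sessions were scheduled and on whether treatment stopped early. Staff who follow the general sentences and staff who follow the restriction could also record differently, both in good faith. A statistical analysis plan cannot repair this, because events never entered in the eCRF cannot be recovered.

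The Long COVID exclusion raises a second question. It rests on the investigator's judgement alone, does not refer to baseline, and says nothing about new or worsened symptoms. Safety and tolerability in these patients is a stated hypothesis (section 2.2), and an unexpectedly high proportion of AEs possibly or probably related to treatment is a ground for stopping the trial (section 5.3, End of Trial). Both draw on the AE record.

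**Working it through.** **Inputs**
- Endpoint time: week 13 (section 4.4.4). Visit 3 window: 13 weeks ± 2, so weeks 11 to 15 (Trial schedule).
- Visit 2 starts within 2 weeks of randomization and ends after the last treatment (Trial schedule).
- Latest treatment: 6 weeks after randomization. Usual course: 2 to 5 sessions a week for 2 to 4 weeks (section 5.2.1, HBO2 SOP). Maximum 10 sessions.

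**The plan's own figure.** Section 8.3 puts week 13 at 7 weeks after the end of treatment. This reproduces with treatment ending at week 6: 13 − 6 = 7.

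**Weeks without recording of non-serious AEs.** If only the treatment period is covered, then

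uncovered weeks = visit 3 week − length of treatment period.

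The start date does not matter, because weeks between randomization and the first session are also outside visit 2. Ten sessions at 5 a week take 10 / 5 = 2 weeks.

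| Treatment period | Visit 3 at week 11 | Week 13 | Week 15 |
|---|---|---|---|
| 6 weeks | 5 of 11 (45%) | 7 of 13 (54%) | 9 of 15 (60%) |
| 4 weeks | 7 of 11 (64%) | 9 of 13 (69%) | 11 of 15 (73%) |
| 2 weeks | 9 of 11 (82%) | 11 of 13 (85%) | 13 of 15 (87%) |

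At the nominal week 13, the smallest gap is 7 weeks. It requires a first session at randomization and a last one at week 6. A subject who starts at week 2 and ends at week 6 has 2 + 7 = 9 uncovered weeks. The time from inclusion to randomization is uncovered as well.

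**From weeks to events.** The documents give no AE rate outside treatment. As an assumption, let that rate be r times the on-treatment rate and let the treatment period last w weeks. Then

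share of non-serious AEs recorded = w / (w + r × (13 − w)).

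- w = 6: r = 1 gives 6 / 13 = 46%; r = 0.1 gives 6 / 6.7 = 90%.
- w = 2: r = 1 gives 2 / 13 = 15%; r = 0.1 gives 2 / 3.1 = 65%.

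The shortfall in events could therefore be small or large. The difference in follow-up between subjects is certain.

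**Symptom overlap.** The synopsis lists, among others, fatigue, headaches, palpitations, shortness of breath and dizziness as Long COVID symptoms. Section 3.2 lists known HBO2 events. Of these five symptoms, only shortness of breath stands in both lists, at 2 per 10,000 treatments. With 40 subjects on HBO2 and 10 sessions each, that is 40 × 10 × 2 / 10,000 = 0.08 expected events.

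**The case against.** The strongest defence is that section 8.3 gives a general rule followed by a headed list of exceptions, and that section 8.3.1 refers only to the AEs that are to be reported. Read this way the scheme is workable and the same in both arms: all AEs during treatment, and SAEs to visit 3. That reading is fair, and it shows that the data have a definite use. It does not deliver the endpoint in section 4.4.4, and it leaves Table 1, the visit 3 procedures and the sentence on registering all AEs out of line with the exceptions.

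A reader might infer that the safety endpoint cannot be measured at all. The documents do not support that, since treatment-period AEs and SAEs to week 13 remain countable. A reader might also take 54% of the weeks as 54% of the events. Section 3.2 counts complications per treatment, which suggests that events may cluster around sessions.

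The most tempting inference is that treatment-induced worsening would never reach the AE table, the DSMB or the stopping criterion. This goes too far:
- The Long COVID exclusion applies only where the investigator judges the symptom to belong to the disease.
- Section 8.2.1 has a possibly-related category for events that underlying disease could also explain.
- The DSMB has access to all trial data and may recommend stopping for any safety concern (section 10.6).
- RAND 36 and EQ-5D are collected at every visit, and significant worsening can be scored as treatment failure (section 6.4).

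None of these routes puts a misattributed symptom into the AE table, so a narrower point stands. Leaving out disease symptoms is not unusual in itself; the gap is the missing rule for new or worsened symptoms.

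The AE comparison is descriptive (section 9.2.6.1), so no formal test is at stake.

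**Conclusion.** The conflict is explicit in the text. As written, non-serious AEs go unrecorded for at least 7 of the 13 weeks after randomization (54%), and for about 11 weeks (85%) with a 2-week course. The endpoint as worded would be under-counted over a window that differs by subject. These figures take visit 3 at its nominal week and read the restriction literally. The share of events lost cannot be derived from the documents; under the assumed rates above, between 15% and 90% of non-serious AEs would be recorded.

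The Long COVID exclusion is a smaller, separate weakness. Some treatment-related worsening may be missing from the AE table, and the documents themselves show overlap for shortness of breath only. They do not show that such worsening would be hidden from the DSMB or from every other record. The primary efficacy analysis and the sample size are not affected.

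**What to change.** Reconcile the synopsis endpoint, section 4.4.4, Table 1, the visit 3 procedures, section 5.2.1 (AE and ADR) and section 8.3 by one of two routes.

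1. **Record to visit 3.** Delete the section 8.3 bullet on non-serious events outside treatment and the matching sentence in section 5.2.1. Align the routine-biochemistry bullet, which would otherwise keep the same restriction for laboratory changes. All AEs are then recorded from inclusion to visit 3, as the endpoint requires.
2. **Keep the short window.** Redefine the endpoint as AEs during the treatment period and SAEs to week 13. Bring the collection sentences, Table 1 and the visit 3 text into line. The endpoint stands under section 4.4 (Secondary endpoints), and section 13 counts a change of secondary variables as substantial.

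In either case, limit the Long COVID exclusion to symptoms present at baseline and unchanged since, and record new or worsened symptoms as AEs with a causality assessment.

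The cost is protocol wording and more AE entries. Under the first route, the entries after treatment fall at a visit that already takes place. If subjects have already passed visit 3 under the present rules, their missing non-serious AEs cannot be restored, and the report should state which rule applied to whom.

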### 8.3.1 Reporting of Adverse Events (AE)

All AEs to be reported shall be registered in the eCRF continuously.

### 8.3.2 Reporting of Serious Adverse Events (SAE)

Serious adverse events are reported to the sponsor on a special SAE form (included in the eCRF) within 24 hours of the investigator being informed of the SAE.

Follow-up information describing the outcome and handling of the SAE is reported as soon as this information is available.

The sponsor will in a timely manner assess whether the adverse event was expected for the investigational product or not, using the reference safety information. Serious AEs must be

|             |                |
|-------------|----------------|
| Trial Code: | HOT-LOCO       |
| Version No: | v.4            |
| Date:       | 2022-01-03     |
| EudraCT No: | 2021-000764-30 |

collected, registered in the CRFs and an assessment of causality of the SAE should be performed. Also, discontinuations due to AEs will be collected.

### 8.3.3 Reporting of Suspected Unexpected Serious Adverse Reactions (SUSAR)

Those SAEs in Sweden which are assessed by the sponsor to be SUSARs are reported via a [CIOMS form](#) to the MPA that are submitting the CIOMS report to the to the European Medicines Agency (EudraVigilance database) according to the specified time frames.

SUSARs that are fatal or life-threatening are reported as soon as possible and no later than 7 days after the incident has become known to the sponsor. Relevant follow-up information is sent thereafter within an additional 8 days. Other SUSARs are reported as soon as possible and no later than 15 days after they have come to the sponsor's knowledge.

Any SUSAR will also be notified to the EPM by the sponsor.

Information about SUSARs occurring during the study is compiled by the sponsor and sent out to the principal investigator at all participating centers in connection to the event.

SUSARs in other participating countries will be reported to respective CA and EC according to applicable procedures

## 8.4 Follow-up of Adverse Events

All AEs should be followed up until they have returned to baseline status or stabilized until End of trial. AEs suspected to have a causal relationship with the trial intervention are followed until recovered or until the subject is on good way to recovery, follow-up will be done at the planned visits regardless of withdrawal from the trial.

## 8.5 Safety Report (Development Safety Update Report, DSUR)

During the trial period an annual Development and Safety Update Report (DSUR) will be submitted to the Swedish MPA and EPM .

The report includes a summary of all reported SAEs and SUSARs, a summarized safety assessment for trial subjects and information regarding potential updates of the risk-benefit assessment since trial approval.

## 8.6 Procedures in case of emergencies, overdose or pregnancy

The sponsor and investigator are obliged to immediately take the urgent safety measures necessary to protect the subjects from immediate danger. Examples of such measures are to temporarily suspend the clinical trial or to introduce supplementary monitoring measures.

|             |                |
|-------------|----------------|
| Trial Code: | HOT-LOCO       |
| Version No: | v.4            |
| Date:       | 2022-01-03     |
| EudraCT No: | 2021-000764-30 |

The sponsor shall inform the MPA and EPM as soon as possible about the urgent safety measures taken by the investigator or sponsor.

If a subject who participates in a clinical trial for investigational products becomes pregnant, this person must be followed up until the birth has taken place. If the fetus/child has any congenital malformation, this must be reported as a serious adverse event or side effect (SAE).

## 8.7 Reference Safety Information

For reference safety information, reference is given in the SmPC.

# 9. Statistics

## 9.1 Statistical Analysis Plan

The principal features of the statistical analysis of the data are described in this section. A more technical and detailed elaboration of the principal features will be written in a separate Statistical Analysis Plan (SAP). The SAP will be finalised prior to Data Base Lock (DBL) and will include a more technical and detailed description of the statistical analyses described in this section. This section is a summary of the planned statistical analyses of the most important endpoints including primary and key secondary endpoints.

Trial Code: HOT-LOCO  
Version No: v.4  
Date: 2022-01-03  
EudraCT No: 2021-000764-30

## 9.1.1 Analysis population

### 9.1.1.1 Definition of Trial Populations

- 9.1.1.1.1 The Full Analysis Set (FAS) Population; All randomized subjects who were exposed at least once to the study intervention will be included in the FAS population.
- 9.1.1.1.2 Per-Protocol (PP) Population; All randomized subjects with no major protocol violations will be included in the PP population. The final decisions regarding the PP population will be taken at the Clean File meeting before the database lock.
- 9.1.1.1.3 Safety Population; All randomized subjects that have received at least one treatment will be included in the safety population.

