| DECT                | Dual Energy Computed Tomography                                                                                             |
| DSMB                | Data Safety Monitoring Board                                                                                                |
| DSUR                | Development Safety Update Report = annual safety report                                                                     |
| ECG                 | Electrocardiogram                                                                                                           |
| eCRF                | Electronic Case Report Form                                                                                                 |
| EndoPAT             | Endothelial assessment of Pulse Amplitude Tonometry                                                                         |
| EPM                 | Etikprövningsmyndigheten (Swedish Ethical Review Authority)                                                                 |
| EPR                 | Electron Paramagnetic Resonance Spectroscopy                                                                                |
| EQ-5D               | EuroQol 5 Dimensions questionnaire                                                                                          |
| FAS                 | Full Analysis Set = including all data from all subjects who have participated in the trial                                 |
| Frändin-Grimby      | Frändin-Grimby activity scale                                                                                               |
| FSS                 | Fatigue Severity Scale                                                                                                      |
| GAD-7               | Generalised Anxiety Disorder 7-item scale                                                                                   |
| GCP                 | Good Clinical Practice                                                                                                      |
| ICF                 | Informed Consent Form                                                                                                       |
| ICH                 | International Council for Harmonization                                                                                     |

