## 7.3 Packaging, labeling, and handling of investigational products(s)

Treatment: 100% oxygen for medical use, cryogenic gas from hospital supply system. There will be no study-specific packaging or labeling.

Placebo: Compressed air from hospital supply system. There will be no study-specific packaging or labeling.

Treatments will be recorded in the eCRF, the code will be unblinded for staff administering the treatments but assessor-blinded. After the subjects end of study, the code will be broken and recorded in the medical records.

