## 7.5 Randomization

Subjects will be enrolled consecutively, as they are found to be eligible for inclusion in the trial, and randomized but after the treatment has been scheduled. Treatment should start within two weeks of randomization.

If a subject discontinues their trial participation, their subject code will not be reused, and the subject will not be allowed to re-enter the trial again. There will be no replacement for these subjects.

Eligible subjects will be randomized in a 1:1 allocation, stratified by disease severity in relation to RAND 36 and gender in blocks (blinded to all study personnel) to either HBO2 or Placebo. There will be a computer generated randomization.

|             |                |
|-------------|----------------|
| Trial Code: | HOT-LOCO       |
| Version No: | v.4            |
| Date:       | 2022-01-03     |
| EudraCT No: | 2021-000764-30 |

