## 7.6 Blinding

This is a double-blind placebo-controlled trial where subjects and all study personnel that participate in the assessment of symptoms and objective findings will be blinded to the treatment. The placebo protocol is well established and even experienced divers cannot differ between “sham treatment” and HBO2 (Lansdorp and van Hulst, 2018). It is not unlikely that some subjects may have problems equalizing the ears even during placebo. Pressure gauges that can be seen by subjects will be covered and all staff will be informed not to discuss the treatment settings when subjects can hear and they will report two air brakes in the same manner as a normal treatment. To validate the blinding process all subjects will be asked at the end of the treatment if they believe they received placebo or HBO2 and AE directly attributed to equalization problems will be compared.

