### 9.2.2 General statistical methodology

Primary and secondary endpoints will be evaluated using the FAS population and sensitivity analyses performed using the PP population.

Trial Code: HOT-LOCO  
Version No: v.4  
Date: 2022-01-03  
EudraCT No: 2021-000764-30

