#### 9.2.8 Handling of Dropouts and Missing Data

For the primary endpoint efficacy analyses, missing data will be adequately imputed for all subjects in the FAS population. In addition, the observed cases population will be evaluated as a sensitivity analysis. For secondary endpoints, only observed data will be analysed.

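### The primary analysis set leaves out randomised subjects who never have a first session, and that exclusion could depend on arm because the staff giving treatment know the allocation

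*Protocol*

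**What the plan says.** Section 9.1.1.1 defines the FAS: "All randomized subjects who were exposed at least once to the study intervention will be included in the FAS population". The Safety population follows in the same list: "All randomized subjects that have received at least one treatment will be included in the safety population". The two rules are in effect the same.

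Section 9.2.2 makes the FAS the main set for efficacy: "Primary and secondary endpoints will be evaluated using the FAS population and sensitivity analyses performed using the PP population". Section 9.2.8 limits the imputation of the primary endpoint to that set: "missing data will be adequately imputed for all subjects in the FAS population". The PP population is narrower still, since section 7.4 asks for at least five treatments.

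The abbreviation list describes the FAS without an exposure condition, as "including all data from all subjects who have participated in the trial".

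On who knows the allocation, section 7.3 says of the code that "the code will be unblinded for staff administering the treatments but assessor-blinded", and section 7.6 says that "subjects and all study personnel that participate in the assessment of symptoms and objective findings will be blinded to the treatment". On timing, section 7.5 places randomisation after the treatment has been scheduled and adds: "Treatment should start within two weeks of randomization". Section 7.5 also rules out replacing subjects who discontinue.

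**The concern.** Dropping randomised subjects who never start treatment is usually tolerated in a blinded trial, because the decision not to start cannot depend on the arm. That argument is weaker here. Between randomisation and the first session there is a period in which some of the people dealing with the subject know the arm, and whether the session takes place decides whether the subject enters the primary analysis.

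If cancellations in that period differed by arm, in number or in kind of subject, the primary comparison would no longer be fully protected by randomisation. The protocol itself foresees randomised subjects who are never treated: section 6.4 places a discontinued subject in the Safety population only if at least one treatment was received. None of the three defined sets would hold such a subject.

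**Working it through.** **1. Is there an all-randomised analysis?** FAS: randomised and exposed at least once. Safety: randomised and treated at least once. PP: at least five treatments and no major violation. A randomised subject with no session is in none of them. Imputation does not bring the subject back, because section 9.2.8 covers FAS subjects only.

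**2. Who could influence a non-start, knowing the arm?**

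| Step | Source | Can it depend on arm? |
|---|---|---|
| First session scheduled | 7.5 (before randomisation); Trial schedule, Visit 1 (randomised when the first treatment is planned) | No |
| Subject changes mind, falls ill or does not attend | 7.6 (subjects blinded) | No |
| Outcome assessor | 7.6, and Visit 1 item c (blinded) | No |
| Session postponed or cancelled, up to two weeks after randomisation | 7.5 (window), 7.3 (treating staff unblinded) | Possible |

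Only the last row leaves a route.

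**3. The plan's own sample size.** Section 9.2.1 uses a difference of 10, SD 15, 80% power and a 5% level; section 9.2.2.2 makes tests two-sided. Exact two-sample t-test power is 79.7% at 36 per group and 80.8% at 37, so the stated 37 is reproduced. The point does not dispute it. With 80 recruited 1:1 there are 40 per arm, and power is 83.8%. Losing 2 subjects from one arm gives 82.8%, and losing 4 gives 81.7%, so loss of power is a minor matter.

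**4. Possible bias (assumed inputs).** The protocol gives no never-treated rate. Suppose *k* of 40 are lost from one arm only, and their mean outcome lies *g* points from that whole arm's mean. The mean of those who remain then moves by

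bias = k × g / (40 − k).

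- k = 2, g = 10: 2 × 10 / 38 = 0.53 points
- k = 4, g = 10: 4 × 10 / 36 = 1.11 points

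With g from 5 to 15, the range is 0.26 to 0.79 points for k = 2, and 0.56 to 1.67 points for k = 4.

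**5. Effect on the false-positive rate.** This takes no true effect, SD 15, one endpoint and an unadjusted two-sided 5% test. The noncentrality is bias / [15 × √(1/(40 − k) + 1/40)].

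- k = 2, g = 10: 0.53 / 3.40 = 0.15, rejection rate 5.3%
- k = 4, g = 10: 1.11 / 3.45 = 0.32, rejection rate 6.2%

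An extreme case of k = 8 and g = 10 gives 2.5 points and 10.7%. It needs a fifth of one arm never to start although treatment was already scheduled, and nothing in the protocol suggests that.

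**The case against.** A reader might infer that the staff who schedule the first session know the allocation. The protocol does not say so. Section 7.3 describes only those administering treatment as unblinded, and initial scheduling comes before or at randomisation. Visit 2 does list a booking step, but without saying who books or whether they know the arm. The discretion given to the responsible physician in section 5.2.1 concerns the frequency and timing of sessions, not whether a subject starts, and that physician is not described as unblinded.

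A reader might also infer that the usual justification for a treated-only set fails outright. That is too strong. A subject's own decision not to start cannot depend on the arm, and both arms have the same session length, maximum number of sessions and six-week limit. The protocol also does not say when in the two weeks the treating staff learn the allocation.

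Further, the trial would make any imbalance visible. Planned treatments not given are recorded with the reason, and an end-of-trial form is required for every randomised subject. A SAP not shown here could add an all-randomised sensitivity analysis. The wording in the abbreviation list is loose, since participation is not defined, and section 9.1.1.1 is the operative text.

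All of this stands, and it limits the point to one narrow route of probably small effect. It does not remove the point. Recording reasons makes an imbalance visible but does not return subjects to the analysis, and an extra sensitivity analysis would leave the primary set in section 9.1.1.1 unchanged.

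**Conclusion.** The FAS excludes randomised subjects who never start, it coincides in effect with the Safety population, and the protocol defines no all-randomised analysis. Because treating staff know the arm during a window of up to two weeks, that exclusion could depend on arm.

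The protocol describes no arm-dependent cancellation, and none is claimed. The effect is zero if everyone starts. Under the assumption of 2 to 4 of 40 lost from one arm, 10 points from that arm's mean, it is about 0.5 to 1.1 points, or 5% to 11% of the 10-point target. These figures are illustrations, not estimates from the protocol. The point merits a change because the rule is stated, the remedy is specific and the cost is low, not because a large bias is expected.

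**What to change.** - Define the FAS in section 9.1.1.1 as all randomised subjects, analysed in their assigned arm.
- Send the week-13 RAND-36 to never-treated subjects who have not withdrawn consent. Visit 3 is timed from randomisation and its questionnaires are digital, and baseline RAND-36 is collected at screening.
- Extend the imputation in section 9.2.8 to all randomised subjects.
- Keep at least one treatment as the rule for the Safety population and for a sensitivity analysis of the primary endpoint.
- Report never-treated subjects by arm with reasons, from the records already required.
- Align the FAS entry in the abbreviation list.

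The cost is wording and a few digital questionnaires; the 37 per group is unchanged. There are two downsides: slight dilution of the treatment effect if several subjects never start, and reliance on imputation for those who withdraw consent before treatment, for whom randomisation is not fully restored. The change should be made before unblinding, so that it cannot look driven by the data.
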